### Data Collection and Statistical Analysis

#### Data Sources

The application of MAM, via the use of IMIDoc incorporates 2 primary sources of information.

First, demographic, laboratory, clinical, and treatment characteristics will be extracted from electronic clinical records during the initial visit.

Second, ePROs recorded by patients participating in the IMIDoc users' arm through the application, as well as those documented by health care personnel during telematic and face-to-face visits through the web application, will be stored in the system's database in a pseudoanonymized and encrypted format.

Access to this data will be restricted exclusively to members of the research team. Data security will be supervised by the data protection officer. All actions performed on the platform will be traceable to the authorized personnel with access to the platform. User authentication tied to role-based security protocols will allow for the effective management of varying access privileges among members of the research team.

#### Data Collection and Schedule for Digital and Face-to-Face Visits

##### Overview

To facilitate understanding, variables are divided into general variables, face-to-face variables, and digital variables (Table 2). General variables correspond to background information captured during baseline visits. Face-to-face variables are captured during in-person visits and are registered in the electronic health record.

**Table 2 table2:** Variables reported in both face-to-face and digital visits.

Dimensions and variables		AR^a^	SpA^b^	Frequency
**ePROs^c^ and disease activity**				
	PGA^d^, VAS^e^, TJC^f^, SJC^g^	✓	✓	Every 15 days
	Enthesis		✓	Every 15 days
	DAS28^h^, HAQ^i^	✓		Monthly
	ASAS-HI^j^, ASDAS^k^, BASDAI^l^		✓	Monthly
**Incidents**				
	Flares, infections, medication problems, and others	✓	✓	By occurrence
**Laboratory and analytical variables**				
	CRP^m^ and ESR^n^	✓	✓	Monthly
**Medication**				
	Medication list and reminders	✓	✓	On demand
	CQR^o^	✓	✓	Monthly
General information about the disease and lifestyle		✓	✓	Every 7 days

^a^RA: rheumatoid arthritis.

^b^SpA: spondylarthritis.

^c^ePRO: electronic patient-reported outcome.

^d^PGA: Patient Global Assessment.

^e^VAS: visual analog scale.

^f^TJC: tender joint count.

^g^SJC: swollen joint count.

^h^DAS28: Disease Activity Score 28.

^i^HAQ: Health Assessment Questionnaire.

^j^ASAS-HI: Assessment of Spondyloarthritis International Society Health Index.

^k^ASDAS: Ankylosing Spondylitis Disease Activity Score.

^l^BASDAI: Bath Ankylosing Spondylitis Disease Activity Index.

^m^CRP: C-reactive protein.

^n^ESR: erythrocyte sedimentation rate.

^o^CQR: Compliance Questionnaire for Rheumatology.

##### General Variables

General variables are those that correspond to clinical records documenting background or baseline information. The following will be collected during baseline visits: demographic variables (sex, age, and BMI); smoking habit; date of diagnosis; serological status for RA, such as rheumatoid factor (RF) anticitrullinated peptide antibodies (ACPA), and histocompatibility antigen (HLA)-B27 for SpA; and treatment information, including start date of current b/tsDMARDs and concomitant therapies such as prednisone, conventional disease-modifying antirheumatic drugs (csDMARDs), and previous treatments.

##### Face-to-Face Variables

Clinical activity and functional capacity will be evaluated according to specific indexes and questionnaires compiled in clinical practice.

For patients with RA, these include the tender joint count (TJC) and swollen joint count (SJC), Disease Activity Score 28 (DAS28), Simplified Disease Activity Score (SDAI), and Health Assessment Questionnaire (HAQ).

For patients with SpA, these include TJC and SJC, Ankylosing Spondylitis Disease Activity Score (ASDAS), Bath Ankylosing Spondylitis Disease Activity Index (BASDAI), Bath Ankylosing Spondylitis Functional Index (BASFI), and Assessment of Spondyloarthritis International Society Health Index (ASAS-HI).

Results from laboratory parameters, such as erythrocyte sedimentation rate (ESR) and C-reactive protein (CRP), are routinely determined in routine clinical practice at each patient visit.

##### Digital Variables and ePROS

For RA patients, the variables include self-assessed tender joint count (sTJC), self-assessed swollen joint count (sSJC), and SDAI. DAS28 will be calculated and managed as patient-derived DAS28 (PtDAS28) and HAQ. Finally, in patients with SpA, the variables include sTJC, sSJC, BASDAI, BASFI, and ASAS-HI.

Health care resource utilization will be documented, including the number of outpatient consultations, emergency visits, drug switches, and nursing and consultant calls. Questions for assessing patient status and treatment tolerance will be recorded. These will include questions such as, “Are you feeling well with the current treatment regimen?” “Have you had symptoms similar to previous outbreaks of your disease?” “If yes, how many outbreaks have you had during the last month?” “Have you experienced any symptoms that you attribute to tolerance problems with the current treatment?” “If yes, please indicate which symptom and to which treatment you attribute it.”
“Have you had any recent fever or infections?” “Have you engaged in any physical activity equivalent to walking for 30 min at least 3 times during the past week?”

To assess the usability of the IMIDoc, questionnaires will collect information regarding willingness, such as the NPS, which evaluates how participants recommend the IMIDo, and follow-up with other patients using the MAM. The System Usability Scale (SUS), consisting of a 10-item questionnaire answered on a scale from 1 to 5 (strongly disagree to strongly agree), will also be used to assess the IMIDoc.

All patients who sign the informed consent form for this project will be invited to participate in a mixed clinical follow-up combining traditional face-to-face visits and home monitoring. The patients will be provided with access to a mobile app that can be downloaded free of charge and that was specially designed in consultation with and under supervision by rheumatologists. The patients will have access to complete questionnaires addressing disease activity, disability, and other domains such as ePROs (Figures 1 and 2). Face-to-face visits will be scheduled at baseline and 6 and 12 months, both for patients included in MAM and for those under the traditional care model.

### Support Resources for Patients

Explanatory material will be provided at the scheduled routine medical visit for all patients included. This explanatory material includes the information required to download the digital solution, the content, and recommendations regarding the frequency with which patients should fill out the questionnaires. Once the patient agrees to be part of the MAM, they will receive a phone call from the digitally partnered clinician to ensure understanding of all the material, clarify doubts, and resolve any issues.

Clinical activity, functional capacity, and overall health will be evaluated according to specific indexes and questionnaires included in IMIDoc, with a predefined frequency for each instrument (alternate assessments of pooled instruments every 15 days, implying a weekly assessment). Reminders with predefined frequencies for each variable will be sent to guarantee their fulfillment.

A messaging and alert system will be available whereby patients can notify their physician of any incidents.

Additionally, the IMIDoc educational material will be provided to patients in a short text format containing information of interest regarding their disease, the different treatments available, and explanatory videos recorded by collaborating rheumatologists.

### Workshops and Tasks for Collaborators

The established collaboration between HULP, HUVH, HUB, HUIL, and HRyC will also act as a facilitator for the development of this study. In fact, web-based meetings have already been held between researchers from all centers to evaluate the resources and the viability of implementing this project. Prior to starting patient recruitment, a web-based meeting will be held with the entire research team to discuss the best way to identify patients and carefully review the methodology that will be followed in the participating centers. Thus, all the information provided to patients will be shared and agreed upon by the centers. Moreover, reminders will be sent to the people responsible for and involved in each project task. In this regard, the clinician in charge of the telematic (digital clinicians) and clinical (onsite clinicians) for each center will be assigned. The incidents recorded in the tool will be periodically reviewed on a web interface by a physician whose clinical work is partly dedicated to this purpose (digital clinician). This professional or another professional from the CTU or biologic clinic (onsite clinician) will contact the patient by telephone to resolve the reported incident. The incident may be resolved completely remotely, or a face-to-face visit may be arranged to address the problem.

### Assessment of Primary and Secondary End Points:

The primary end point will be an at least 20% reduction in face-to-face visits compared to visits carried out in the previous year. This reduction in face-to-face visits will be driven by the number of incidents that can be resolved telematically, the number of total interactions, and the number of ePROS that patients complete during the follow-up period that allows us to assess adherence and telematic monitoring.

The secondary end points will be assessed by tracking the number of accesses and time per access to the digital solution per patient to assess adherence. Agreements between the patients' self-assessment and clinician assessment will be assessed to compare face-to-face visits at 6-month intervals with the closest assessment in the digital solution. We will also measure the proportion of patients in remission or low disease activity according to the activity index every 6 months. Usability and satisfaction perceived by patients will be assessed by the SUS NPS.

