### MAM Explanation

All patients with RMDs treated with biological or targeted disease-modifying antirheumatic drugs (b/ts-DMARDs) are followed up in the immune-mediated disease (IMID) unit. This is a structured care unit comprising a multidisciplinary team of rheumatologists and specialized nurses. All care actions are protocolized, and face-to-face IMID unit visits of patients with RMDS under b/ts-DMARDs are recorded in a database. Based on the objectives described, a theoretical protocol was drawn up on how to implement a mixed model combining face-to-face visits with telematic follow-up. The MAM protocol [17] is a care model that incorporates a digital mobile app that patients can use at home and professionals can review asynchronously to detect incidents and monitor clinical evolution between face-to-face visits (Figure 1 depicts a flowchart escribing the participant inclusion in the study and subsequent steps). This protocol considers the role of each of the professionals in the unit, how face-to-face and telematic follow-up is carried out, and how to act according to the response to prescribed treatment.

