#### Participants

A total of 360 patients will be enrolled in the clinical study, comprising the group receiving MAM intervention and the control group, following the traditional care model matched by age and sex (Table 1). The inclusion criteria for patients in the MAM group are as follows: (1) adult patients >18 years; (2) patients with RA or SpA under treatment with b/tsDMARDs followed in the complex therapy unit (CTU); and (3) patients with an available smartphone. The exclusion criterion includes patients with conditions that hinder or prevent the use of a mobile app (eg, blindness, developmental delay, dementia, and digital illiteracy).

**Table 1 table1:** Patients at each hospital treated with the MAM^a^ or a traditional care model.

Hospital	Patients in the MAM (n=280), n			Patients in the traditional care model (n=80), n	
	RA^b^	SpA^c^	RA		SpA
HULP^d^	40	40	10		10
HURyC^e^	30	30	10		10
HUVH^f^	30	30	10		10
HUIL^g^	20	20	5		5
HUB^h^	20	20	5		5

^a^MAM: mixed attention model.

^b^RA: rheumatoid arthritis.

^c^SpA: spondylarthritis.

^d^HULP: Hospital Universitario La Paz.

^e^HURyC: Hospital Universitario Ramón y Cajal.

^f^HUVH: Hospital Universitario Vall.

^g^HUIL: Hospital Universitario Infanta Leonor.

^h^HUB: Hospital Universitario Bellvitge.

All patients from outpatient consultations treated with b/tsDMARDs for at least 6 months will be invited to participate in the study. Those who have been invited but have declined will be registered, and then if they accept, will be enrolled in the study. The control group will be formed by patients with the same treatments and similar sociodemographic and clinical characteristics.

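### The primary visit end point is judged only against the previous year, so a 20% fall, or its absence, cannot by itself be attributed to the MAM

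*Protocol article*

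**What the plan says.** In the protocol article, the section Assessment of Primary and Secondary End Points defines the target as follows: "The primary end point will be an at least 20% reduction in face-to-face visits compared to visits carried out in the previous year". The same paragraph names the cause: "This reduction in face-to-face visits will be driven by the number of incidents that can be resolved telematically", together with total interactions and completed ePROs. The control group is not mentioned there.

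Digital Variables and ePROS sets the follow-up schedule: "Face-to-face visits will be scheduled at baseline and 6 and 12 months, both for patients included in MAM", and the sentence goes on to apply the same schedule to the traditional care group. Workshops and Tasks for Collaborators allows further visits: "The incident may be resolved completely remotely, or a face-to-face visit may be arranged to address the problem".

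Table 1 (Participants) gives 280 MAM patients and 80 patients in traditional care, the latter matched by age and sex. Objectives ties the comparison with conventional follow-up to clinical outcomes, as the fourth secondary objective. Data Analysis lists paired and unpaired tests but assigns none to visits.

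On visit records, MAM Explanation says that "face-to-face IMID unit visits of patients with RMDS under b/ts-DMARDs are recorded in a database". Digital Variables and ePROS says that "Health care resource utilization will be documented, including the number of outpatient consultations, emergency visits, drug switches, and nursing and consultant calls".

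The article does not give the previous-year visit rate, and it does not say whether the baseline visit counts.

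**The concern.** The MAM is meant to reduce face-to-face visits, yet part of the follow-up count is set by the protocol and is the same in both groups. That count is compared with a year in which the study schedule did not apply. The change therefore combines three things: any effect of the MAM, any difference between earlier routine scheduling and the study schedule, and any general trend over time. A before/after figure in MAM patients cannot separate them.

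The article nevertheless gives the fall a cause. If the target is met, the MAM may be credited with a change that controls on the same schedule would also show. If it is missed, the MAM may be judged to have failed because scheduled visits left no room for a 20% fall.

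**Working it through.** **Inputs from the protocol article**
- Threshold: 20% reduction (Assessment of Primary and Secondary End Points).
- Scheduled follow-up visits S: 2 if only months 6 and 12 count, 3 if baseline counts too (Digital Variables and ePROS).
- Groups: 280 MAM and 80 controls (Table 1). The 15% loss in Participants leaves 0.85 × 280 = 238 and 0.85 × 80 = 68.

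**Assumptions, because the article gives no figure**
- Previous-year visits b: 2 to 4 per year.
- Overdispersion: 1 (Poisson) to 2.
- Scheduled visits are attended.

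The article has no visit-rate figure to reproduce. Its crude sample size of 300 rests on a precision argument without a visit rate, and this point does not depend on it.

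**Step 1: schedule alone, with no MAM effect and no unscheduled visits.** Change = (S − b)/b.

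| b | S = 2 | S = 3 |
|---|---|---|
| 2 | 0% | +50% |
| 3 | −33% | 0% |
| 4 | −50% | −25% |

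A 20% fall needs S ≤ 0.8b, so b ≥ 2/0.8 = 2.5 without baseline, or b ≥ 3/0.8 = 3.75 with it. At b = 3, the unstated rule on the baseline visit moves the result from −33% to 0%.

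**Step 2: room for unscheduled visits.** The average number of unscheduled visits compatible with a 20% fall is 0.8b − S.
- S = 2: −0.4 at b = 2; 0.4 at b = 3; 1.2 at b = 4.
- S = 3: −1.4 at b = 2; −0.6 at b = 3; 0.2 at b = 4.

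A negative value means that the target cannot be reached even if every incident is resolved remotely. A positive value means that a 20% fall appears whenever unscheduled visits stay below it, whether or not the MAM is the reason.

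**Step 3: what a comparison with controls does.** Suppose no MAM effect, 2 follow-up visits in each group, and prior rates of 4 (MAM) and 3 (controls). Dividing the two before/after ratios gives (2/4)/(2/3) = 0.75, a spurious 25% reduction. The direct follow-up ratio is 2/2 = 1. With non-randomised controls, the follow-up ratio adjusted for prior visits is therefore the safer form.

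The shared floor still dilutes it. If controls have 2 scheduled and 0.5 unscheduled visits, removing every unscheduled visit gives 2/2.5 = 0.80. If controls have 3 visits, a ratio of 0.8 means 2.4 visits, so unscheduled visits must fall from 1 to 0.4, or by 60%.

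**Step 4: precision at an assumed 3 visits per year, Poisson, after 15% loss.**
- MAM before/after: SE of the log rate ratio = √(2/(238 × 3)) = 0.053.
- Ratio of before/after ratios, MAM to control: √(2/(238 × 3) + 2/(68 × 3)) = 0.112. For a ratio of 0.8, |ln 0.8|/0.112 = 0.223/0.112 ≈ 2.0, so power is roughly 50%.
- Follow-up ratio, MAM to control, at 0.8: √(1/(238 × 3 × 0.8) + 1/(68 × 3)) = 0.082, with power about 78%. This falls to about 61% and 49% at overdispersion 1.5 and 2.
- Over 2 to 4 visits per year and overdispersion 1 to 2, power for the follow-up ratio is about 35% to 89%.

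These are rough guides, because a Poisson model treats scheduled visits as random.

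**The case against.** The strongest defence is that this is an exploratory implementation study. The main objective in Objectives is to evaluate implementation, Participants calls the trial exploratory, and a before/after count is a recognisable measure of utilisation. The unpaired tests in Data Analysis do not exclude a control comparison, and a fuller document might specify one. This limits the point but does not remove it: the article itself fixes the previous year as the comparator, sets a success threshold and names the cause of the fall.

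Four stronger readings are tempting, and the documents do not support them.
- *A reader might infer that the schedule decides the result automatically.* It does not. Incident visits can be arranged, so the schedule is a floor, and unscheduled visits can undo a schedule-driven fall. The earlier routine schedule is not described either. Care in the IMID unit is already protocolised, and six-monthly visits, including the baseline visit, may be usual practice.
- *A reader might infer regression to the mean.* No mechanism is stated. All outpatients treated for at least 6 months are invited, without selection on visit count or disease activity.
- *A reader might infer that visits are ascertained differently in the two years.* Listing resource use under a digital heading does not show this. Face-to-face visits are recorded in a unit database, and nothing says that the source changes.
- *A reader might infer that dividing by the control change removes the shared schedule.* Step 3 shows that this fails when prior rates differ, and that a common floor dilutes the ratio in any case.

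**Conclusion.** The point holds in a limited form. As defined, the primary end point cannot on its own support the cause that the article gives for it. "Uncontrolled" describes this end point, not the study, which has 80 concurrent controls.

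The size depends on a previous-year rate that the documents do not give. With no MAM effect and no unscheduled visits, the illustrated change runs from +50% (2 prior visits, baseline counted) to −50% (4 prior visits, baseline not counted). A 20% fall is out of reach below 2.5 prior visits per year if baseline is not counted, and below 3.75 if it is, provided that scheduled visits are attended. Above those rates a fall can arise without the MAM, but unscheduled visits may prevent it. Which case applies in this population cannot be determined from the article.

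**What to change.** The visit schedule itself need not change; the change concerns how visits are counted and compared.

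1. Judge the visit end point against the concurrent controls. One suitable form is the follow-up visit rate ratio of MAM to control from a count model that allows for overdispersion, adjusted for prior-year visits, centre, diagnosis, age and sex. Keep the MAM before/after change as descriptive.
2. Exclude the baseline study visit from both windows, and state the window limits so that the 12-month visit is treated alike for everyone.
3. Count unscheduled visits separately from protocol-scheduled visits in both groups, because the shared floor dilutes a ratio of total visits.
4. As a precaution, take visits for both years and both groups from the same hospital or IMID-unit record, and confirm that it is available at all five hospitals.

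No new patients or visits are needed. The costs are an amended primary end point after recruitment has begun, extraction of prior-year visits for the 80 controls, and lower precision: a standard error of about 0.11 against 0.053 for the ratio of before/after ratios at an assumed 3 visits per year under Poisson, and more with overdispersion. The adjusted follow-up ratio should lose less, but its power may still be modest. Confounding will remain, because the controls are not randomised and the only matching factors named are age and sex. The report should say so.

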### Objectives

The main objective is to evaluate the implementation of a conceptual framework for a hybrid care model called the mixed attention model (MAM) for use in clinical practice.

The secondary objectives are as follows: (1) to identify features associated with adherence to follow-up through the MAM; (2) to evaluate the technological acceptance of the digital solutions included in the MAM; (3) to assess the agreement between patient-reported join assessments and clinician-based join assessments; (4) to evaluate whether the implementation of the MAM improves clinical outcomes compared to conventional follow-up; and (5) to assess patients´ health literacy using a digital interface.

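### In the MAM arm only, nothing keeps the examining rheumatologist from seeing patients' own joint counts before scoring the joints

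*Protocol article*

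**What the plan says.** All references are to the protocol article.

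- **End point.** Assessment of Primary and Secondary End Points names "the proportion of patients in remission or low disease activity according to the activity index every 6 months", without naming the index or who scores it. The same section compares visit assessments at 6-month intervals with the nearest app assessment, to measure patient-clinician agreement (secondary objective 3).
- **Comparison served.** Secondary objective 4 is "to evaluate whether the implementation of the MAM improves clinical outcomes compared to conventional follow-up". The abstract places this in the main objective.
- **Indices at visits.** Face-to-Face Variables lists DAS28 and SDAI for RA, and ASDAS and BASDAI for SpA. Data Analysis names DAS28 or BASDAI, but only as the baseline covariate.
- **Indices in the app.** For RA there are self-assessed tender and swollen counts and SDAI, and "DAS28 will be calculated and managed as patient-derived DAS28 (PtDAS28) and HAQ". For SpA, "in patients with SpA, the variables include sTJC, sSJC, BASDAI, BASFI, and ASAS-HI". That list omits ASDAS, which Table 2 shows as monthly.
- **Access.** MAM Explanation has professionals reviewing app data asynchronously between visits. Development of the Digital Health Solution gives rheumatologists web access to what patients record.
- **Where data are kept.** Data Sources refers to ePROs entered by patients and "those documented by health care personnel during telematic and face-to-face visits through the web application". The Overview of the visit schedule says "Face-to-face variables are captured during in-person visits and are registered in the electronic health record".

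**The concern.** A joint count is a judgement, and the study is open. In the control arm the examiner counts joints without any app record. In the MAM arm the same kind of examiner may have a series of the patient's own counts on screen. An examiner who has just read that the patient marked certain joints may look harder at them, or settle a doubtful joint in line with the entry.

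Two results are exposed. The agreement analysis assumes two separate readings and will look better than it is if one reading informed the other. The remission or low-activity comparison with controls could move in one arm because of how the joints were scored and not because of the care model. This is the only disease-activity end point named in the end-point section.

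Neither problem can be repaired once the visits have taken place, so it cannot be left to an analysis plan.

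**Working it through.** **1. Is the exposure in one arm only?** Data Sources ties patient entry in the app to the IMIDoc users' arm, and controls follow the traditional model. Self-counts therefore exist only for MAM patients.

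**2. Will self-counts be available at the visit?** Table 2 sets tender and swollen counts every 15 days. With full adherence, about 182/15 ≈ 12 entries exist by the 6-month visit and 365/15 ≈ 24 by the 12-month visit.

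**3. Does anything prevent the examiner from reading them first?** MAM Explanation and Development of the Digital Health Solution grant access. Workshops and Tasks for Collaborators separates digital from onsite clinicians, but lets either contact the patient about an incident and does not bar one person from both roles. No section sets the order of examination and review, or keeps the examiner unaware of the entries.

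**4. Effect on agreement.** Let D be the self-count minus the count the clinician would have made unaided. If the clinician moves a fraction w of the way toward the self-count, the recorded difference is (1 − w)D. The mean difference and its SD both shrink by the factor 1 − w. The document gives nothing from which to estimate w.

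**5. Effect on the arm comparison.** The direction depends on the patients. If they count more joints than the examiner would, MAM clinician scores rise and fewer MAM patients reach remission or low activity. If they count fewer, the reverse holds.

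**6. Scale.** The document gives no figure for this end point, so there is none to reproduce. The illustration below uses:
- group sizes from Table 1: 280 MAM and 80 control, of which 140 and 40 have RA;
- alpha .05 from Data Analysis, taken as two-sided;
- assumed: no true difference, control proportion 50 to 80%, and an artefact of 5 or 10 points in either direction in the MAM proportion. Matching and losses are ignored.

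With control proportion p and n1 patients, and MAM proportion q and n2 patients, let pb = (n1·p + n2·q)/(n1 + n2). Then:
- SE0 = √[pb(1 − pb)(1/n1 + 1/n2)]
- SE1 = √[p(1 − p)/n1 + q(1 − q)/n2]
- P(P<.05) = Φ[(δ − 1.96·SE0)/SE1] + Φ[(−δ − 1.96·SE0)/SE1], with δ = |q − p|

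Worked case, RA only, p = 0.60, q = 0.70:
- pb = (24 + 98)/180 = 0.678
- SE0 = √(0.2184 × 0.03214) = 0.0838
- SE1 = √(0.006 + 0.0015) = 0.0866
- first term: Φ[(0.100 − 0.164)/0.0866] = Φ(−0.74) ≈ 0.229; second term ≈ 0.001; total ≈ 0.23

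| Comparison | 5-point artefact | 10-point artefact |
|---|---|---|
| RA only, 40 vs 140 | 8.5 to 13.5% | 20 to 41% |
| All patients, 80 vs 280 | 12 to 20% | 35 to 65% |

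RA patients are half of each group. A 10-point artefact confined to RA is therefore 5 points in the pooled comparison, and the 12 to 20% cell applies. With no artefact the rate is the nominal 5%.

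**The case against.** The strongest reply is that the document already points to a like-for-like comparison. Face-to-face visits take place at baseline, 6 and 12 months in both groups, which fits a six-monthly end point. The app score has its own name, PtDAS28, and agreement is a separate end point. This stands. A reader might infer that MAM patients will be classified from app scores and controls from clinician scores, especially since Support Resources for Patients speaks of evaluating activity by the indexes in IMIDoc. No passage says so, and visit scoring in both arms is the natural reading.

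Other replies also carry weight:
- The choice of index and its cut-offs are details that an article may leave to the full protocol or analysis plan. Taken alone, they are no finding.
- For SpA, BASDAI appears under the same name at visits and in the app, with no separate clinician version. The concern is mainly about RA.
- Data Sources and the Overview need not conflict, because the former's subject is ePROs. However, Table 2 groups joint counts under ePROs and disease activity, so the place of recording is ambiguous.
- Access is not proof that examiners look first, and reviewing app data is part of the model under study.

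The last reply does not dispose of the point. The care model can include review of app data while the outcome examination at three scheduled visits comes before it. Nothing in the document provides for that.

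**Conclusion.** The text does not secure an independent clinician assessment that is made in the same way in both arms. In the MAM arm alone, the examiner may read self-counts before scoring joints. This may inflate patient-clinician agreement and may affect the remission or low-activity comparison, mainly in RA.

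The size and direction are unknown. The percentages above show only what an assumed artefact would do to the false-positive rate and are not estimates for this study. The document does not support saying that the comparison is unlike, that it favours MAM, or that any given share of patients would be reclassified. This is a cheap improvement to make while visits remain to be done.

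**What to change.** 1. **Order of steps.** Instruct sites that the examining rheumatologist records tender and swollen joint counts before opening the patient's IMIDoc record at the baseline, 6- and 12-month visits.
2. **Source and index.** In Assessment of Primary and Secondary End Points, state that remission or low disease activity is taken in both arms from the face-to-face assessment at 6 and 12 months, with one prespecified index per disease. Use the same index for the baseline adjustment in Data Analysis, which now names DAS28 or BASDAI.
3. **App scores.** Reserve PtDAS28 and the other app scores for agreement and monitoring.
4. **Recording.** Clarify in Data Sources and the Overview where face-to-face joint counts are entered, so that entering them does not require opening the self-counts first.

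The cost is some wording and one site instruction, with no extra assessor or test. The order of steps at the visit changes slightly, and app data cannot stand in for a missed visit. The instruction stops exposure at the visit itself. It does not erase what an examiner remembers from reviewing entries between visits, and the report should say so.
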